Beyond static neurophysiological measures, the integration of perception and action represents a relevant framework for understanding exercise-related adaptations in real-life contexts. Dual-task paradigms, which reflect everyday functional demands, may be particularly sensitive to changes induced by dance-based interventions. The theoretical interpretation of these mechanisms, including their relation to stimulus–response integration models such as the Binding and Retrieval in Action Control (BRAC) framework, is further addressed in the expected mechanisms section.

Previous research supports the feasibility and effectiveness of relatively short-duration (six weeks) exercise interventions in FM. In this regard, Casanova-Rodríguez et al. [16] reported that statistically significant differences can be observed in aerobic exercise programs lasting from three to twenty-four weeks, and this duration range has also been applied in strength training interventions [17]. Taken together, these findings suggest that a six-week intervention period is enough to produce clinically meaningful changes and is supported by evidence in the FM literature.

However, despite growing evidence supporting the benefits of creative dance-based and multicomponent exercise interventions in fibromyalgia, no previous studies have simultaneously examined their effects on physical performance under single- and dual-task conditions together with resting-state EEG markers of neuroplasticity, particularly alpha and theta activity. Overall, these findings support the use of a multidimensional intervention combining strength training and creative dance to target both physical and cognitive impairments in individuals with FM, forming the basis for the purposes of the present study.

Objectives:(a)To analyze the effects of a 6-week physical exercise training program based on creative dance combined with strength training on physical fitness (strength, mobility, balance, functional capacity, and gait agility) under both single- and dual-task conditions in individuals with FM;(b)To investigate exercise-related changes in resting-state brain electrical activity and HRV as a secondary outcome, with a primary focus on beta power, in order to explore potential neurophysiological mechanisms underlying functional improvements.

Hypotheses:

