**H1.** Six weeks of strength training and creative dance are expected to significantly improve physical fitness (strength, mobility, balance, functional capacity, and gait agility) in individuals with FM, under both single- and dual-task conditions, compared with their baseline status and a control group.**H2.** It is hypothesized, for exploratory purposes, that the physical exercise intervention will be associated with specific changes in resting-state brain electrical activity, characterized primarily by increased beta power, that could be related to increased cerebral blood flow [13]. Also, the autonomic modulation would be enhanced [18].

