Participants will be seated in a quiet room with their feet flat on the floor and eyes open and instructed to remain quiet for five min to acquire baseline resting Electroencephalography (EEG) and Heart Rate Variability (HRV) data. During this procedure, an adhesive electrode (Kendall™ H1224SG, CardinalHealth™, Dublin, OH, USA) will be placed in the left lower thoracic region, below the breast area, over the intercostal space corresponding to the cardiac region, to record cardiac activity. EEG and HRV will be recorded using the Enobio^®^ system instrument (Neuroelectrics, Cambridge, MA, USA) with the NIC2 software, version 2.1.4.1 (for Windows) [47]. This equipment has demonstrated high reliability, even with dry electrodes [48]. EEG activity will be obtained from 19 channels following the international 10–20 system, covering frontal (Fz, Fp1, Fp2, F3, F4, F7, and F8), central (Cz, C3, and C4), temporal (T3, T4, T5, and T6), parietal (Pz, P3, and P4), and occipital (O1 and O2) areas, using the mastoids as references. Impedance will be maintained below 10 kΩ. Signals will be sampled at 500 Hz, applying a 50 Hz notch and a 1–40 Hz bandpass filter. For data processing during movement tasks, recommendations from Cheron et al. [49] will be followed, applying an Artifact Subspace Reconstruction (ASR) filter [50]. Preprocessing and analysis will be performed in EEGlab (v2021, Matlab toolbox; San Diego, CA, USA), where artifacts from ocular, muscular, or electrical sources will be removed using Independent Component Analysis (ICA) [51]. Cleaned data will then be divided into spectral bands: theta (4–7 Hz), alpha-1 (8–10 Hz), alpha-2 (11–12 Hz), beta-1 (13–18 Hz), beta-2 (19–21 Hz), and beta-3 (22–30 Hz) using the pop_spectopo.m function.

HRV signals will be exported in .edf format and analyzed with Kubios HRV software (version 2.1) [52]. The extracted metrics will include: (a) time-domain variables—mean HR, RR, SDNN, Pnn50, and rMSSD; (b) frequency-domain indices—low frequency (LF)/high frequency (HF) ratio (LF/HF) and total power; and (c) nonlinear parameters—approximate (ApEn) and sample entropy (SampEn).

Stimulus–Response Paradigm

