EEG measures were included as secondary, exploratory outcomes. Although an exploratory hypothesis regarding changes in beta power was formulated based on previous literature [57], EEG analyses were not designed as confirmatory and were conducted to generate mechanistic insights. To reduce the number of comparisons and improve statistical power, regions of interest (ROIs) were defined as a priori by grouping electrodes according to anatomical location: frontal (Fp1, Fp2, F3, F4, and Fz), central (C3, C4, and Cz), and parietal (P3, P4, and Pz). Mean spectral power was computed for each frequency band within each ROI by averaging across electrodes. For exploratory analyses, a 2 × 2 factorial design implemented within the EEGLAB STUDY framework was used to examine EEG data before and after the intervention in alpha and theta bands. Permutation-based statistical testing with 2000 iterations was applied, and multiple comparisons were controlled using the false-discovery rate (FDR) correction.

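### Resting beta power is the stated EEG target, but the only EEG-specific before/after analysis names alpha and theta, and no analysis of resting beta is explicitly specified

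*Protocol article*

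**What the plan says.** The Introduction sets objective (b) as the study of resting brain electrical activity and HRV "as a secondary outcome, with a primary focus on beta power". H2, stated to be exploratory, predicts EEG change "characterized primarily by increased beta power" and adds a second part: "Also, the autonomic modulation would be enhanced". The Discussion repeats the beta focus and the expected increase. Earlier in the Introduction, however, the gap in the literature is described in terms of "resting-state EEG markers of neuroplasticity, particularly alpha and theta activity".

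Section 2.12.2 splits the resting signal into six bands: theta, alpha-1, alpha-2 and three beta sub-bands (13–18, 19–21 and 22–30 Hz).

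Section 2.13 restates the beta hypothesis, says that the EEG analyses are not confirmatory, and defines frontal, central and parietal regions of interest. It then says: "Mean spectral power was computed for each frequency band within each ROI by averaging across electrodes". The inferential step is a 2 × 2 design in EEGLAB STUDY, with 2000 permutations and FDR correction, which "was used to examine EEG data before and after the intervention in alpha and theta bands". Beta is not mentioned in that step.

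**The concern.** The plan states a direction for one resting EEG quantity, beta power, and then fixes its EEG-specific before/after test on other bands. This is more than detail left to a fuller document. The article does say which bands are tested, and they are not the bands of its own hypothesis, which is restated in the same part of Section 2.13.

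At stake is the reading of the EEG result. If resting beta has no contrast fixed in advance, an analyst can choose the sub-band, the region and the model after seeing the data, and a reader cannot tell whether a reported beta increase is the hypothesised one or a selected one. Conversely, a null or positive alpha/theta result would not bear on what H2 predicts for EEG.

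**Working it through.** There is no stated figure to reproduce: the sample size was set on fibromyalgia impact, not on EEG. The check sets the passages side by side and adds a count.

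**Step 1. Target against test**

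| Place | Resting EEG band named |
|---|---|
| Introduction, evidence gap | alpha and theta |
| Introduction, objective (b) | beta (primary focus) |
| Introduction, H2 | beta (increase) |
| Section 2.12.2, extraction | theta, alpha-1, alpha-2, beta-1, beta-2, beta-3 |
| Section 2.13, restated hypothesis | beta |
| Section 2.13, regional averaging | every band |
| Section 2.13, 2 × 2 permutation test | alpha and theta |
| Discussion | beta (primary focus, increase) |

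Beta is the only resting band given a direction, and it is absent from the test row.

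**Step 2. Does another analysis supply the beta contrast?**

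- *Stimulus–response analysis (Section 2.12.2).* It includes beta, there defined as 12–30 Hz, but the signal is recorded during a task. The comparisons are between types of step and between levels of task load. It is not resting-state, not before/after, and not by trial arm, so it does not address H2.
- *General mixed model (Section 2.13).* It has fixed effects for group, time and group × time, with random intercepts for associations and participants. It excludes no outcome, and residual checks are described for all variables. Regional beta power could enter it as an ordinary per-participant outcome. But the paragraph opens with the physical performance tests and never mentions EEG or HRV, while EEG gets its own later paragraph with different software, inference and error control. If the model does cover EEG, alpha and theta have two analyses and nothing says which governs. Even then, no beta sub-band or region is named.

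**Step 3. Count of what is left open**

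- Resting bands × regions: 6 × 3 = 18 measures.
- Covered by the alpha/theta test, if alpha-1 and alpha-2 are kept apart: 3 × 3 = 9.
- Beta measures without a named EEG-specific before/after contrast: 3 × 3 = 9.

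Section 2.13 does not say whether the two alpha sub-bands are kept apart. If they are merged, the alpha/theta test has 2 × 3 = 6 measures. The beta count does not change.

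The permutation sentence does not itself say resting state. I read it so because it follows directly on the banded regional averages, whose bands are those of the resting-state processing.

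**The case against.** The strongest counter-argument is the general mixed model. It is worded broadly, beta power is computed for every region, and Benjamini–Hochberg adjustment is stated for the trial as a whole. On that reading resting beta does have a group × time test, and the permutation analysis is only an addition for two other bands. This part stands: the documents do not rule it out. They do not say it either, and they leave the beta measures unspecified.

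A reader might therefore infer that H2 is never tested. The documents do not support that. The mixed model may be meant to cover beta, and H2 also has an autonomic part that the alpha/theta sentence does not concern. What can be said is that no analysis of resting beta is explicitly specified.

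A reader might also want to attach a false-positive rate to the nine beta measures. Any such rate would need independent, uncorrected tests. Neighbouring sub-bands and regions in the same women would be expected to correlate, and the plan states FDR and Benjamini–Hochberg control, so I give none.

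Finally, the past-tense verbs in Section 2.13 might suggest that the EEG data already exist. Section 2.2.2 places recruitment between January and March 2026, and the recording and band-splitting are described in the future tense. The mixed tenses do not show that data have been collected.

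It is also fair to say that EEG is declared secondary and exploratory throughout, and that the limitations section concedes limited robustness for it. This lowers the weight of the point but does not remove the mismatch.

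**Conclusion.** The point holds in this form: the plan's stated EEG target is resting beta power, its only EEG-specific before/after analysis is stated for alpha and theta, and no contrast for resting beta is explicitly specified. Nine of 18 band-by-region measures, the nine to which the directional hypothesis refers, are left without a named EEG-specific test. The Introduction adds to the inconsistency by describing the evidence gap in terms of alpha and theta.

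The conclusion rests on two readings: that the permutation sentence concerns resting data, and that the silence of the mixed-model paragraph on EEG leaves its scope undetermined. If that model was meant to cover EEG, the defect narrows to an unstated scope and unnamed beta measures, and the same edit cures it.

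The consequence is ambiguity and room for selective reporting within an exploratory analysis. No primary outcome, sample size or confirmatory inference depends on it, so it should be corrected but is below must-fix.

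**What to change.** Amend the EEG paragraph of Section 2.13 as follows:

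1. Name resting beta power as the lead exploratory EEG contrast, with the beta summary fixed in advance. It can be power over 13–30 Hz (three measures, one per region) or beta-1, beta-2 and beta-3 separately (nine measures), in the frontal, central and parietal regions. Either is acceptable. A plain average of the three sub-bands is not the same as 13–30 Hz power, because their widths differ, so the text should say which is meant.
2. Test it by the group × time interaction in the mixed model of Section 2.13, with participants nested within associations. That model reflects allocation by association, whereas no association effect is described for the EEGLAB 2 × 2 analysis. Simply adding beta to the permutation analysis would therefore leave the clustering out.
3. Apply FDR control over the stated beta measures, and keep alpha and theta as a separate exploratory family.
4. State whether the other EEG measures and HRV also go through the mixed model, and if so which analysis governs for alpha and theta.
5. In the Introduction, reconcile the alpha/theta description of the evidence gap with the beta focus of objective (b) and H2.

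The cost is a few sentences. Beta extraction and regional averaging are already specified, so no new measurement is needed.

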#### 2.2.2. Recruitment

The sample size will be calculated based on one of the study’s primary outcomes, i.e., the impact of FM. Data from a previous study [22] that will be used as a reference evaluated the effects of a creative dance intervention on this outcome. In that study, the impact of FM was reduced by 1.16 points compared with the control group after six weeks of intervention.

According to the results obtained in the G*Power statistical power analysis software version 3.1.9.7 (Heinrich Heine University Düsseldorf, Düsseldorf, Germany), assuming an effect size of f(V) = 0.98, a power of 85%, and a significance level of 0.05, a sample size of 22 people per intervention group is estimated. However, considering an anticipated dropout rate of 10%, a total of 44 participants (22 per group) will be needed to observe a significant effect.

Therefore, the participants recruitment will take place between January and March 2026. Both groups will consist of women with FM (exercise group: *n* = 22; and control group: *n* = 22) recruited from different FM associations in the region of Extremadura.

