### 2.4. Clusters Randomization

The clusters in this study are FM associations from the region of Extremadura (Cáceres, Almendralejo, Hervás, and Olivenza) in Spain. Each association will be randomly assigned to either the intervention group, which will participate in a structured physical activity program, or to the control group. The allocation sequence for the associations will be created using a computer-generated random number system (Random Number Generator tool; Google, LLC., Mountain View, CA, USA). Simple randomization will be applied, with no stratification, given the small number of clusters. The sequence will be recorded in a password-protected Excel file. Personnel responsible for enrolling associations and implementing the intervention will remain blinded to the allocation sequence until each cluster is assigned. The principal investigator (IP) will provide the group assignment immediately prior to the start of the intervention for each association, ensuring allocation concealment.

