### 2.13. Data Analysis

The collected outcomes will be compiled in an anonymized database for statistical processing. Both descriptive statistics and inferential analyses will be conducted. Data analysis will be performed using the Statistical Package for the Social Sciences software (SPSS, version 25.0; IBM Corp., Armonk, NY, USA). The Shapiro–Wilk and Kolmogorov–Smirnov test will be used to assess the normality of all variables.

Furthermore, to explore the effect of physical exercise intervention, physical performance tests will be analyzed under both single task and dual-task conditions. Dual-task cost will be calculated to quantify the impact of performing a cognitive task on physical performance. Given the cluster-randomized design, changes over time and between-group differences were analyzed using linear mixed-effects models, accounting for the hierarchical structure of the data, with participants nested within fibromyalgia associations. Group (intervention vs. control), time, and their interaction (group × time) were included as fixed effects. Random intercepts were specified for associations and for participants, and random slopes were included when appropriate, assuming an unstructured covariance matrix. The normality of model residuals was visually assessed for all variables.

To quantify the degree of clustering, the intra-cluster correlation coefficient (ICC) will estimate from the variance components of the mixed-effects models, calculated as the ratio of between-association variance to total variance (between-association plus residual variance). This parameter will be used to evaluate the magnitude of within-association dependence and to confirm the appropriateness of the cluster-adjusted analytical approach.

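### The EEG alpha/theta permutation test ignores that only four associations are randomised, so its between-arm p-values can be too small

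*Protocol article*

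**What the plan says.** Section 2.4 of the protocol article defines the randomised units: "The clusters in this study are FM associations from the region of Extremadura (Cáceres, Almendralejo, Hervás, and Olivenza) in Spain". Allocation is by association: "Each association will be randomly assigned to either the intervention group, which will participate in a structured physical activity program, or to the control group". It is unrestricted: "Simple randomization will be applied, with no stratification, given the small number of clusters". Section 2.2.2 plans 44 women, 22 per arm.

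Section 2.13 draws the consequence for changes over time and between-group differences. It prescribes linear mixed models, "accounting for the hierarchical structure of the data, with participants nested within fibromyalgia associations", and plans to estimate the intra-cluster correlation.

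Later in the same section EEG receives its own procedure for the alpha and theta bands: "a 2 × 2 factorial design implemented within the EEGLAB STUDY framework was used to examine EEG data before and after the intervention". The inference is then fixed: "Permutation-based statistical testing with 2000 iterations was applied, and multiple comparisons were controlled using the false-discovery rate (FDR) correction". No association term is given, and permutation is not restricted to whole associations. The two factors and the permuted unit are not named. The section also states the status of this work: "EEG analyses were not designed as confirmatory and were conducted to generate mechanistic insights".

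**The concern.** A permutation test of a randomised intervention takes its validity from re-drawing the allocations that could have occurred. Here these are re-assignments of four associations. Shuffling individual women instead tests whether women are exchangeable across associations and arms, which is a stronger hypothesis than no effect of the programme on EEG power.

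The two hypotheses separate when the women of one association change together between visits for reasons other than the programme. Such a shared change falls wholly on one arm, and an individual-level test reads it as an arm difference. The plan recognises this dependence for its mixed models, yet the EEG procedure as written does not carry it over. At stake are the p-values and FDR-based significance claims for between-arm alpha and theta contrasts, which feed the trial's mechanistic discussion.

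**Working it through.** **Inputs from the protocol article.** Four associations, simple randomisation (section 2.4); 44 women, 22 per arm (section 2.2.2); 2000 permutations with FDR (section 2.13); alpha 0.05 (section 2.13). The 2000 is a chosen setting, so there is no derived figure to reproduce.

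**Assumptions.** The 2 × 2 is read as group × time. Tests are two-sided. Each association contributes 44/4 = 11 women, two associations per arm. The documents give no intra-association correlation (ICC) of the post-minus-pre change, so a range is shown.

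**Step 1: allocations available.**
- All: 2^4 = 16.
- Both arms filled: 16 − 2 = 14.
- Two associations per arm: C(4,2) = 6.

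With a symmetric statistic, the smallest two-sided p of an association-level permutation is 2/16 = 0.125, 2/14 = 0.143 or 2/6 = 0.33. None reaches 0.05, even before FDR. Individual shuffling offers C(44,22), about 2.1 × 10^12 splits, and 2000 draws allow p as small as 1/2001, about 0.0005. A setting of 2000 therefore makes sense only for shuffling below the association level.

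**Step 2: false-positive rate of one test.** Simulated with no intervention effect: change = association effect (variance ICC) + individual error (variance 1 − ICC); women's changes shuffled 2000 times; 3000 simulated trials. As a cross-check, the variance of the arm difference is inflated by about 1 + (11 − 1) × ICC, so the rate is roughly P(|Z| > 1.96/√inflation).

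| Assumed ICC of change | Inflation | Approximate rate | Simulated rate, 2:2 | Simulated rate, 1:3 (22 vs 7, 7, 8) |
|---|---|---|---|---|
| 0 | 1.0 | 5.0% | 4.8% | 4.7% |
| 0.02 | 1.2 | 7.4% | 7.1% | 7.9% |
| 0.05 | 1.5 | 11.0% | 10.9% | 13.6% |
| 0.10 | 2.0 | 16.6% | 17.2% | 20.1% |
| 0.20 | 3.0 | 25.8% | 28.6% | 33.5% |

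The 1:3 column is included because simple randomisation permits that split.

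**Step 3: does FDR help?** Take six tests (three regions × two bands, an assumption) with Benjamini–Hochberg and individual errors correlated 0.5 across tests. At ICC 0.20 the chance of at least one false discovery is about 50% if association shifts also correlate 0.5 across tests, and about 33% if one shift is common to all six. At ICC 0.10 the corresponding figures are about 25% and 19%. The correction works on p-values that are already too small, so it does not restore the nominal rate.

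**The case against.** The strongest reply is that EEG is secondary and declared non-confirmatory, that section 4.3 already warns about the robustness of the EEG findings, and that four clusters limit every outcome in this trial. That is why the severity is low. It does not make a between-arm p-value valid, and the plan does apply formal error control to these tests.

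Four stronger readings are tempting, and the documents do not support them.

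- *The EEG hypothesis itself is compromised.* The permutation test is stated for alpha and theta. The EEG hypothesis concerns beta, and the association-nested mixed model of section 2.13 is written without excluding EEG, so it may well cover beta.
- *Every difference between associations counts as an effect.* A stable difference cancels in the post-minus-pre contrast; only association-specific change remains. A purely within-woman time contrast does not use the allocation and is unaffected. The article does not report that recording conditions differ by association.
- *The plan states that individuals are shuffled.* It does not. This is inferred from 2000 iterations against at most 16 allocations and from the absence of any restriction. The inference is strong, and a fuller analysis plan may settle it.
- *A valid test here has a smallest p of 0.33.* That holds only for a 2:2 split, which section 2.4 does not guarantee.

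**Conclusion.** The point holds for the between-arm alpha and theta contrasts. As written, the EEG test departs from the cluster adjustment that the same section calls for. If individuals are shuffled, its false-positive rate passes twice nominal from an ICC of change of about 0.05 and reaches about 28% at 0.20 with two equal associations per arm. With six tests and FDR, the chance of a false discovery at 0.20 is about 33% to 50%. These sizes rest on an assumed ICC, association size and number of tests; at an ICC of zero the test keeps its level. No primary outcome is affected, so this is a low-severity correction.

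**What to change.** In the EEG paragraph of section 2.13:

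- Name the two factors of the 2 × 2 design and the permuted unit.
- Do not use individual-level permutation p-values or FDR significance for between-arm EEG contrasts.
- For each region and band, report the between-arm difference in post-minus-pre change with an interval that respects the associations. It can come from the association means, or from the section's own mixed model with a small-sample degrees-of-freedom correction (itself weak with four clusters).
- Show the four association means and label the result descriptive.
- If an association-level permutation is kept, state its smallest two-sided p for the scheme used: 0.125 over 16 allocations, 0.143 over 14, or 0.33 if 2:2.

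Changing the permuted unit alone is no remedy, since none of these floors reaches 0.05.

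The cost is one rewritten paragraph, with no new data, women or visits. The price is wide intervals and no between-arm significance claim for these EEG outcomes, which fits their stated exploratory status.
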